### Methods

A prospective, randomized double-blind trial will be conducted at the National Cancer Institute (INCA - HCIII), in Rio de Janeiro, Brazil. All patients will be provided with written informed consent form prior to study enrolment. Eligible patients are female aged between 18-70 years of age with an ASA physical status of one to three, with body mass index equal to or greater than 30 kg / m2, scheduled to undergo elective breast surgery. The exclusion criteria are: patients who had received chemotherapy within 4 weeks, patients who have undergone emergency surgery, with known history of vomiting within 24 hours; a known hypersensitivity to other 5-HTantagonists, patients who received any antiemetic, corticosteroid, or other drug with antiemetic effect, smokers and patients with a history of alcoholism.

Using computer-generated random numbers, the patients will be assigned into one of the two treatment groups on the morning of surgery. Forty patients will be randomized to receive a bodyweight-adjusted dose of 1mcg/kg of palonosetron (group I - GI) and another forty patients will receive a fix dose of 75 μg of palonosetron (group II - GII). Each study drug will be mixed with saline to a total volume of 10 ml in an unlabelled syringe and will be intravenously administered just prior to induction of anesthesia. All patients, surgeons, anesthesiologists involved in the study will be blinded to group allocation to maintain the double-blind conditions.

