The secondary outcome will be to evaluate the frequency of polymorphism of the 5-HT3 receptors and their correlation with the antiemetic effect and adverse effects. The patients will have cell samples of the oral cavity, collected through smear. The collected material will be placed in a tube and then will be stored at freezer. Then, it will be analyzed in the laboratory of Clinical Research Unit at the Federal Fluminense University (UFF). After extracting the DNA from the samples using a DNA purification kit, a polymerase chain reaction (PCR) will be performed for analysis of single nucleotide polymorphisms. Biological samples will be discarded at the end of the analysis.

Sample size was calculated with reference to the results of a study comparing weight-adjusted doses of palonosetron for prevention of PONV in laparoscopic gynaecological surgery in no-obese patients. For a P value of 0.05 and a power of 0.8, a minimum of 36 per dose group was required. To allow for possible dropouts, the aim was to recruit 40 patients in each group.

GraphPad Prism 4.0® (GraphPad Softwares Inc., San Diego, CA, USA) will be used for statistical analysis. The Wilcoxon signed rank 2x2 test will be use to ensure that data will be normally distributed. Patient characteristics and intra- and post-operative variables will be analysed by Unpaired Student´s t-test. Proportions will be compared using x^2^ square or Fisher’s exact test. A P value < 0.05 is considered statistically significant.

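### Between-arm t-tests of patient characteristics are uninformative after randomisation; describing baseline and adjusting for age and ASA class fixed in advance would be a modest improvement on the unadjusted tests

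*Protocol*

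**What the plan says.** The last paragraph of the protocol's Methods section sets the analysis. "Patient characteristics and intra- and post-operative variables will be analysed by Unpaired" Student's t-test, so baseline characteristics share one sentence and one test with intra-operative and post-operative variables. "Proportions will be compared using" the chi-square or Fisher's exact test. The threshold is common to all: "A P value < 0.05 is considered statistically significant".

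The natural reading is that the second sentence governs the efficacy proportions, such as incidence of nausea, need for rescue and complete response. Both tests it names are unadjusted. The paragraph mentions no covariate and no adjusted model, and the randomisation paragraph mentions no stratification. Nor does the protocol rule out adjustment.

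Eligible patients are "female aged between 18-70 years of age with an ASA physical status of one to three". Age and ASA class are therefore known for every patient before allocation and are free to vary between arms.

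**The concern.** A significance test between randomised arms asks whether a baseline difference could have arisen by chance. Here it must have, because chance made the allocation. The test therefore examines a null hypothesis known to be true. It also does not measure what matters, which is whether an imbalance sits on a factor that predicts nausea and vomiting.

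In a trial of 80 patients this misleads in both directions. A fairly large imbalance on a prognostic factor can be non-significant and remain in an unadjusted comparison. A trivial difference on an irrelevant factor can be significant. At stake are the accuracy of the efficacy estimate in the particular randomisation obtained, and a few points of power in a trial planned at 80%.

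**Working it through.** **Inputs from the protocol (Methods).** 40 per arm; significance level 0.05 (sidedness not stated, two-sided assumed); "For a P value of 0.05 and a power of 0.8, a minimum of 36 per dose group was required"; no event rates, effect size or prognostic strengths.

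**The plan's own figure.** The minimum of 36 per group cannot be verified without event rates. It is attainable: 45% against 15%, two-sided, power 0.80, no continuity correction, gives 36. Raising it to 40 matches 10% dropout: 36/(1 − 0.10) = 40.

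**What a baseline test lets through at 40 per arm.**
- Continuous factor: the largest non-significant observed difference is t(0.975, 78 df) × √(2/40) = 1.991 × 0.2236 = 0.445 SD (0.470 SD at 36 per arm).
- Binary factor: 12/40 against 20/40 has pooled proportion 32/80 = 0.40 and standard error √(0.40 × 0.60 × 2/40) = 0.1095, so z = 0.20/0.1095 = 1.83 and P = 0.07. Fisher gives P = 0.11.
- Chance of a gap of 20 points or more, in either direction: 6.7% at 30% prevalence, 9.3% at 50%.
- False alarms: with 5 to 10 independent baseline tests (number assumed), 1 − 0.95^5 = 23% to 1 − 0.95^10 = 40%.

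**Shift in the crude risk difference from a 20-point imbalance, no treatment effect.** The outcome odds ratio of the factor is assumed. Centring the risks on 50%, p1 = √OR/(1 + √OR), p0 = 1 − p1, and the shift is 0.20 × (p1 − p0).

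| Assumed OR | p1 − p0 | Shift |
|---|---|---|
| 2 | 0.172 | 3.4 points |
| 3 | 0.268 | 5.4 points |
| 5 | 0.382 | 7.6 points |

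**Simulation over all randomisations.** 4,000 trials per setting, 40 per arm, one binary factor at 50% prevalence; treatment odds ratio 1 for type I error and 0.25 for power; Pearson chi-square against logistic regression on arm and factor.

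| Assumed OR | Type I error, unadjusted / adjusted | Power, unadjusted / adjusted |
|---|---|---|
| 2 | 5.8% / 5.2% | 80% / 80% |
| 3 | 5.8% / 5.0% | 78% / 79% |
| 5 | 5.4% / 5.0% | 72% / 77% |

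In the roughly 500 simulated trials per setting with a 15 to 20 point imbalance, unadjusted type I error was 6.2%, 7.6% and 8.0%. The simulation error is about √(0.05 × 0.95/500) = 1 point, so the first of these is not distinguishable from 5%.

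**Other assumed settings.** With a 50% control rate, a benefit of about 30 points, a factor at 40% prevalence with odds ratio 2.7 to 4.5, and age at −0.3 to −0.5 log-odds per SD, power rises from 82%, 81% and 76% to 86%, 84% and 82%, a gain of 3 to 6 points. With age alone the gain is 1 to 2 points. Across the settings tried, the average gain is thus about 0 to 6 points.

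**The case against.** The strongest reply is that the planned outcome tests are valid. An unadjusted chi-square or Fisher test of randomised arms is standard, and the simulation keeps its type I error near 5%. Covariates are also often left to a statistical analysis plan, which is not at hand, so their absence from the protocol is not itself a fault. Both points stand. What remains open to comment is what the protocol does state: t-tests of patient characteristics, and unadjusted tests as the only named methods for proportions.

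Eligibility also narrows the room for imbalance, since sex, smoking status, a BMI of at least 30 and recent vomiting are restricted. That stands too, although age and ASA class still vary.

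Three stronger readings are tempting and are not supported.
- A reader might infer that baseline P values will be used to declare the arms balanced or to decide on adjustment. The protocol contains no such rule.
- A reader might take the difference detectable with 80% power, 2.80 × √(2/40) = 0.63 SD, as the size of imbalance that slips through. That figure concerns a true population difference, which is zero here. Any observed difference above about 0.445 SD would be flagged.
- A reader might quote the power after an adverse 12/40 against 20/40 split: 57% to 71% unadjusted against 83% to 85% adjusted in the settings with a factor at 40% prevalence. A gap at least that large in that direction arises in only about 4.3% (binomial) to 5.5% (hypergeometric) of trials at that prevalence. Favourable imbalances are as likely.

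**Conclusion.** The point holds as a modest improvement in precision and in protection against conditional bias. The baseline t-tests are stated in the protocol and are uninformative. The unadjusted efficacy tests are valid but can be bettered at little cost. It would be wrong to conclude that the primary comparison is invalid.

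The 3 to 8 point shift and the 0 to 6 point power gain rest wholly on assumed event rates, prevalences and prognostic odds ratios, because the protocol gives none. The gain from age and ASA class together was not simulated. Age alone gives 1 to 2 points, and the prognostic strength of ASA class in this population is unknown, so the lower part of the range is the safer expectation. The results cover binary outcomes only. The primary outcome also includes the number of emetic episodes and the analgesic requirement, to which these figures do not apply.

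**What to change.** In the statistical paragraph of Methods:

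1. Remove patient characteristics from the t-test sentence and state that they will be presented by arm descriptively, without P values.
2. Analyse each binary efficacy outcome by logistic regression on randomised arm, age (continuous) and ASA class. Fix the covariates and the coding of ASA class in advance, and do not choose them by a balance test.
3. Report the standardised (marginal) risk difference with its confidence interval.
4. Keep the chi-square or Fisher test as a sensitivity analysis.

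Optionally, previous postoperative nausea and vomiting or motion sickness could be a third covariate. The protocol does not mention recording it, so this needs one yes/no item on the case report form.

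The cost is a few sentences and software that fits logistic regression. The number of events limits the model to two or three covariates: at an assumed 50% against 20%, for example, there would be 20 + 8 = 28 events. ASA class is therefore best entered as a single term. The expected gain is modest.

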**Abstract/Summary:**

BACKGROUND: Palonosetron is a second generation serotonin antagonist usually used in a ﬁxed dose of 75 mcg for the prophylaxis of postoperative nausea and vomiting. Although there are a few trials evaluating bodyweight-adjusted doses of palonosetron, the ideal dose for obese patients has not yet been investigated. The aim of this study is to evaluate if the use of bodyweight-adjusted doses of palonosetron (1mcg / kg) is more effective than a fixed dose (75mcg) on preventing postoperative nausea and vomiting in female patients with a body mass index equal to or above 30 kg /m2 whom have undergone breast surgery

METHODS: A prospective, randomized double-blind trial will be conducted at the National Cancer Institute (INCA - HCIII), in Rio de Janeiro, Brazil. Eligible patients are female aged between 18-70 years of age with an ASA physical status of one to three, with body mass index equal to or greater than 30 kg / m2, scheduled to undergo elective breast surgery. Forty patients will be randomized to receive a bodyweight-adjusted dose of 1mcg/kg of palonosetron (group I - GI) and 40 patients will receive a fix dose of 75 μg of palonosetron (group II - GII). Patients will be assessed over 4 time periods: 0-1h, 1-6 h, 6-24 h and 24-48 h after surgery. After discharge, all patients will be contacted by telephone at regular intervals to record the episodes of nausea and vomiting as well as analgesic and antiemetic requirements. The primary outcome measure will include the number of emetic episodes, the incidence of nausea, the need for rescue antiemetics and the analgesic requirement over 48h. The secondary outcome will be to evaluate the frequency of polymorphism of the 5-HT3 receptors and their correlation with the antiemetic effect and adverse effects.

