**Aims & Objectives**

Our hypothesis for this study is that the use of bodyweight-adjusted doses of palonosetron (1mcg / kg) is more effective than a fixed dose (75mcg) for preventing postoperative nausea and vomiting in female patients with a body mass index equal to or above 30 kg / m2 whom have undergone breast surgery.

Primary objectives:

1. To determine the frequency of individual episodes of nausea in the periods of 1, 6, 24 and 48 hours postoperatively
2. To determine the frequency of individual episodes of vomiting in the periods of 1, 6, 24 and 48 hours postoperatively
3. Compare need of antiemetic rescue medication during the periods of 1, 6, 24 and 48 hours postoperatively
4. Determine the number of patients who had complete antiemetic response (absence of nausea, vomiting and need for rescue medication).

Secondary objectives: To evaluate the frequency of polymorphism of the 5-HT3 receptors and their correlation with the antiemetic effect and adverse effects

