All patients will receive premedication with midazolam. Intraoperative monitoring included electrocardiography, blood pressure measurement, peripheral oxygen saturation (SpO2), and end-tidal CO2 tension (ETco2). General anesthesia was induced using 1,5 mg/kg of propofol, 3 μg/kg of fentanyl, 1,5 mg/kg of lidocaine and 0.3 mg/kg of rocuronium. Then the insertion of laryngeal mask will be performed and the pulmonary ventilation will be maintained with 6 ml/kg of ideal-weight and maximum peak pressure 25 cmH2O. The anesthesia will be maintained with sevoflurane in 50% oxygen/air. Sevoflurane concentration was adjusted to ensure an equal depth of anesthesia during surgery as assessed by the bispectral index (BIS; BIS A-1050 Monitor, Aspect Medical Systems, Newton, MA, USA), which will be held between 40-60. Remifentanil will be administered for supplemental intraoperative analgesia and its dose will be adjusted to maintain blood pressure and heart rate within 20% of baseline values. At the end of surgery, residual neuromuscular blockade will be reversed with 2mg/kg of Sugammadex and the laryngeal mask will be removed. Patients will stay on the postanesthetic care unit for at least 1 hour before going to the ward. In the postoperative recovery room, the haemodynamic variables along with postoperative complications such as shivering, hypotension, dizziness, constipation or any other adverse reaction to the drug will be recorded by a blinded observer. After surgery, rescue medication will be intravenous metoclopramide (10 mg) for more than one episodes of nausea or vomiting.

All episodes of nausea and vomiting will be recorded for 48h. Patients will be assessed over 3 time periods: 0-6 h, 6-26 h and 24-48 h after surgery. After discharge, all patients will be contacted by telephone at regular intervals to record the episodes of nausea and vomiting as well as analgesic and antiemetic requirements. The primary outcome measure will include the number of emetic episodes, the incidence of nausea, the need for rescue antiemetics and the analgesic requirement after 48h. Nausea is deﬁned as a subjective unpleasant sensation associated with the urge to vomit without expulsion of gastric content and vomiting is deﬁned as the forceful expulsion of gastric contents trough the mouth.

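### One superiority hypothesis, two differing sets of primary outcomes, no decisive endpoint, and a flat P < 0.05 as the only decision rule

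*Protocol*

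**What the plan says.** **Hypothesis.** Protocol, Aims & Objectives: weight-adjusted dosing "is more effective than a fixed dose (75mcg) for preventing postoperative nausea and vomiting". This is one directional claim, and it is not tied to a particular endpoint.

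**Primary objectives (same section).** There are four. The first concerns nausea and reads "To determine the frequency of individual episodes of nausea in the periods of 1, 6, 24 and 48 hours postoperatively". The second asks the same of vomiting, with the same four time points. The third concerns rescue and is the only one worded as a comparison: "Compare need of antiemetic rescue medication during the periods of 1, 6, 24 and 48 hours postoperatively". The fourth is a count of complete responders, meaning patients free of all three events, and it carries no time window.

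**Primary outcome in the Abstract and Methods.** Both say "The primary outcome measure will include the number of emetic episodes, the incidence of nausea, the need for rescue antiemetics and the analgesic requirement", the Abstract over 48 h and Methods after 48 h. This set adds analgesic requirement and leaves out complete response.

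**Periods.** The Abstract says "Patients will be assessed over 4 time periods: 0-1h, 1-6 h, 6-24 h and 24-48 h after surgery". Methods instead gives three periods: 0-6, 6-26 and 24-48 h.

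**Decision rule (end of Methods).** "A P value < 0.05 is considered statistically significant". Proportions are to be compared by chi-square or Fisher's exact test. No order of testing, multiplicity adjustment or success rule is given.

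**Sample size (Methods).** At P = 0.05 and power 0.8, 36 per group are required, raised to 40 for dropouts. The endpoint, event rates and effect size are not given.

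**The concern.** A single 5% error rate belongs to a single test. Here one claim is attached to many results, each called primary and each judged against the same threshold. Nothing in the protocol prevents an isolated result, such as nausea in one window, from being offered as support for the superiority claim when the doses do not differ. Because the sections disagree about what is primary, the choice of headline result could also be made after the data are seen. At stake is a dosing conclusion for obese patients drawn from 80 women.

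**Working it through.** **Step 1. The plan's own figure.** The 36 per group can be neither confirmed nor refuted, because no rates are given. With the usual two-proportion formula (two-sided 0.05, power 0.80), an assumed 45% vs 15% fits:

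n = [1.96 × √(2 × 0.30 × 0.70) + 0.842 × √(0.45 × 0.55 + 0.15 × 0.85)]² / 0.30² = (1.270 + 0.515)² / 0.09 ≈ 35.4, so 36.

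Other pairs fit equally well, for example 60% vs 25% with continuity correction. The step from 36 to 40 matches 10% dropout: 36 / 0.90 = 40. The figure therefore does not reveal which endpoint was meant, and it uses one undivided alpha of 0.05.

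**Step 2. Count the primary comparisons.**
- Aims & Objectives: 3 outcomes × 4 time points + complete response = 13.
- The same objectives with the three periods in Methods: 3 × 3 + 1 = 10.
- The Abstract and Methods outcome set, read once over 48 h: 4.

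**Step 3. Error if any one significant result counts as success.** For k independent tests the two-direction rate is 1 − 0.95^k. Counting only results that favour weight-adjusted dosing, it is 1 − 0.975^k. The correlated columns come from a Monte Carlo run with equally correlated z-tests, counting both directions.

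| k | Both directions, independent | Both, correlation 0.5 | Both, correlation 0.7 | Both, correlation 0.9 | Favouring weight-adjusted only, independent |
|---|---|---|---|---|---|
| 4 | 18.5% | 15.5% | 13.0% | 9.3% | 9.6% |
| 10 | 40.1% | 28.6% | 21.4% | 12.7% | 22.4% |
| 13 | 48.7% | 33.5% | 24.0% | 13.7% | 28.0% |

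The benchmark for one test is 5% in both directions and 2.5% in one.

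**Step 4. Check with binary data.** Null simulations used 40 per arm, 13 tests, and assumed event rates and within-patient correlation.
- One model had correlated nausea, vomiting and rescue in each window. It gave 21-30% with Fisher's exact test and 34-52% with uncorrected chi-square.
- A second model had a patient-level tendency to symptoms and tied rescue to episode count. It gave 15-23% with Fisher and 39-46% with uncorrected chi-square. Using Fisher only where an expected count was below 5 gave 23-36%.
- In the second model, counting only results that favour weight-adjusted dosing gave about 8-12% with Fisher and 20-24% with chi-square.
- With cumulative windows the two-direction rates were 14-19% (Fisher) and 28-34% (chi-square). With event rates halved they were 9-16% and 28-42%.
- A single complete-response test stayed at about 2-6%.

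**Step 5. Cost of adjusting across everything instead.** Bonferroni over 13 tests uses 0.05 / 13 = 0.0038. For an assumed 50% vs 20%, power at 36 per group falls from about 77% to about 41%, and the required n rises from 39 to 69 per group.

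**The case against.** The strongest replies are these.

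- **The protocol never says that one significant window is success, and never uses the word unadjusted.** This is true. It gives one general threshold and is silent on how the results combine. A reader might infer that the plan declares success on any of 13 tests, but the text does not say so. The error rates above are conditional on that use of the results. What stands against the plan is that no other success rule is written.
- **Only the third objective says that groups are compared; the others speak of determining.** This is also true, but the hypothesis is comparative, the trial is randomized, and Methods says that proportions will be compared.
- **Thirteen is only one reading.** Accepted: 10 or 4 can also be defended, and the time points may be cumulative.
- **The largest figures count both directions and assume independence or uncorrected chi-square.** Accepted. A significant result favouring the fixed dose would not support the hypothesis. Counting one direction lowers the absolute rate, but its benchmark falls to 2.5% as well, so the relative inflation remains.
- **A statistical analysis plan could supply an adjustment.** It could, and such detail is properly left there. But this protocol itself labels several outcomes primary, in two sets that do not match, so the defect is in what it fixes and not in what it omits.

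**Conclusion.** The point holds: the protocol has several primary outcomes in two non-matching sets, names no decisive endpoint, and offers a flat 0.05 as its only rule. If any significant primary result is taken as success, the two-direction family-wise error is roughly 13% to 49%. Under independence it is 18.5%, 40% or 49% for 4, 10 or 13 tests, and it is lower with correlation or Fisher's exact test. In the direction of the hypothesis, 13 independent tests give 28% against 2.5%.

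These sizes rest on assumed event rates and correlations. Extreme assumptions reach slightly outside the range: about 9% with four tests at correlation 0.9, or with rare events and Fisher's test, and 52% in one chi-square scenario.

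A reader might conclude that the trial's false-positive rate is close to one half. The documents do not support that as a fact: it requires 13 tests, independence or uncorrected chi-square, and counting results in either direction. What does hold in every scenario run is that the two-direction rate exceeded 5%.

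**What to change.** 1. Name one primary endpoint and use it identically in the Abstract, Aims & Objectives and Methods. Complete response, already defined in the fourth objective, is a natural choice once a 0-48 h window is added. Test it once at two-sided 0.05 and declare success on it alone. Another single endpoint, or an ordered or adjusted set, would also control the error.
2. Move the other outcomes and all period-specific comparisons to secondary. Report them with estimates and 95% confidence intervals, or test them in a fixed order or with Holm adjustment.
3. Reconcile the three-period and four-period schedules, and state whether analgesic requirement is primary or secondary.
4. State which endpoint and event rates gave 36 per group. If the chosen primary endpoint differs, restate the power for it.

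The cost is protocol wording and a short power check. No new data are needed, since nausea, vomiting and antiemetic requirements are already to be recorded. A single primary endpoint needs no increase in sample size for multiplicity, but whether 40 per group suits that endpoint cannot be judged until item 4 is done. The change should be made before unblinding. The small downside is that an isolated significant window can no longer be claimed as a primary result.
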